### Statistical analysis plan

We prespecify the following primary endpoints: [1] overall survival from registry enrolment; [2] organ-specific progression (e.g., incident heart failure, renal failure) defined by laboratory, imaging, and electrophysiological standard clinical criteria (e.g., N-terminal pro B-type natriuretic peptide or reduction of ejection fraction in echocardiography for heart failure, creatinine clearance for renal failure, neurofilament light chains and nerve conduction studies for neuropathy progression, and further as detailed in the subtype-specific sections in the Study Protocol); and [3] longitudinal quality-of-life scores. Secondary endpoints include subtype-specific trajectories and treatment-specific outcomes. Survival endpoints will be calculated using Kaplan–Meier and Cox models; when competing risks are relevant (e.g., cause-specific events), Fine–Gray models will be used. Longitudinal continuous outcomes (biomarkers, PROMs) will be analysed with linear mixed-effects or generalised estimating equations. For comparative effectiveness questions, we will adjust for confounding using multivariable regression and propensity score methods (matching/weighting); the a priori covariate set includes age, sex, subtype, baseline stage/organ involvement, and key comorbidities (DAG-informed).

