Missing data will be addressed by multiple imputation by chained equations (MICE) under a MAR assumption; results will be pooled with Rubin’s rules and compared with complete-case analyses in sensitivity checks. We control multiplicity for primary endpoints (e.g., Holm/Bonferroni) with α = 0.05 (two-sided). Interim analyses are descriptive only. Based on current referral volumes, we anticipate enrolment of ~20–30 patients/year; over five years (N ≈ 100–150), precision for a 10% event rate is ±~6% (95% CI). Analyses will be performed in R; code and analysis manifests will be shared with the de-identified data release. To address time-dependent exposures, treatment status will be modelled as a time-varying covariate using episode splitting, in which each patient’s follow-up is partitioned into consecutive intervals reflecting their actual exposure status at each point in time. Immortal-time bias will be addressed by classifying all person-time prior to treatment initiation as unexposed, ensuring that the pre-treatment observation window is not misattributed to the treated state. Since treatment switches most commonly occurr in the context of clinical progression, they will be handled by opening a new interval at the date of the switch, with exposure updated accordingly to reflect the new treatment, while prior intervals retain their original classification. Treatment discontinuation will be handled analogously, with patients reclassified as unexposed from the discontinuation date onward. Where dose-level data are available, dose changes will be treated by the same mechanism.

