We acknowledge two limitations inherent to a routine-care registry setting. First, treatment event dates are recorded at clinical visits rather than to the exact calendar day; interval boundaries therefore carry a degree of temporal imprecision. Second, the frequency and timing of follow-up visits are clinically driven rather than protocol-fixed, which may result in treatment changes between visits not being captured with full precision. To quantify the potential impact of the first limitation, a sensitivity analysis applying a ± 4-week uncertainty window around documented treatment event dates will be conducted. As a further sensitivity analysis, a landmark approach will be applied at 6 and 12 months, classifying patients by treatment status at the landmark and restricting follow-up accordingly; as this approach avoids immortal-time bias by design rather than by statistical adjustment, convergence of results with the primary analysis will serve as an indicator of robustness. Given these constraints, comparative effectiveness estimates derived from time-dependent Cox proportional hazards models should be interpreted as exploratory and hypothesis-generating rather than causal.

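### Stopping and switching are coded with no method for the progression that may drive them, so time-dependent Cox hazard ratios can be biased in either direction, even for a drug with no effect

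*Protocol article*

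**What the plan says.** All of this stands in the Statistical analysis plan section of the protocol article.

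- **Exposure.** For survival comparisons, "treatment status will be modelled as a time-varying covariate using episode splitting". Person-time before initiation counts as unexposed.
- **Switching.** The reason is given first: "Since treatment switches most commonly occurr in the context of clinical progression". The response is to open a new interval, "with exposure updated accordingly to reflect the new treatment, while prior intervals retain their original classification".
- **Stopping.** "Treatment discontinuation will be handled analogously, with patients reclassified as unexposed from the discontinuation date onward". No lag is stated, and there is no separate state for patients who were treated earlier.
- **Adjustment.** "we will adjust for confounding using multivariable regression and propensity score methods (matching/weighting"). The listed variables follow: "the a priori covariate set includes age, sex, subtype, baseline stage/organ involvement, and key comorbidities (DAG-informed").
- **Sensitivity analyses.** A window of ±4 weeks around treatment dates addresses date imprecision. Landmarks at 6 and 12 months address immortal time, and for these "convergence of results with the primary analysis will serve as an indicator of robustness".
- **Limitations.** Two are named: imprecise treatment dates and clinically driven visits. Given these, the time-dependent Cox estimates are to be read as exploratory rather than causal.

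**The concern.** Episode splitting allocates person-time correctly. It does not deal with the reason why exposure changed. If a patient stops because the disease has progressed, the high-risk time that follows enters the unexposed group. If a patient starts, or switches onto a drug, because of progression, the high-risk time enters that drug's group. Progression after enrolment is then a common cause of exposure and death. A baseline covariate, or a propensity score built from baseline covariates, cannot capture it.

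The plan recognises the link for switches but names nothing to handle it, and informative treatment change is not among its limitations. At stake are the treatment-specific outcomes, which are secondary endpoints. A reader given a hazard ratio and an agreeing landmark analysis would be told that the result is robust, when both could carry the same confounding.

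**Working it through.** **The plan's own figure.** The plan gives no number on this point. Its only computed figure is the precision for a 10% event rate: 1.96 × √(0.1 × 0.9 / 100) = 0.059 and 1.96 × √(0.1 × 0.9 / 150) = 0.048. The stated ±~6% holds at the lower end of the sample-size range. Nothing below depends on it.

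**Mechanism.** Let progression multiply the death hazard by k, and let the drug do nothing. Let p1 and p0 be the shares of exposed and unexposed patients at risk who have progressed. The apparent ratio at that time is

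[1 + (k − 1) p1] / [1 + (k − 1) p0].

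It equals 1 only if p1 = p0. Stopping on progression raises p0 and lowers p1, so the ratio falls below 1. Starting on progression raises p1, so it rises above 1. With k = 5 the expression is (1 + 4 p1)/(1 + 4 p0), which can take values from 1/5 to 5.

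**Simulation.** There was one run of 60,000 patients per scenario, with 60 monthly steps and a true hazard ratio of 1.00 for both death and progression. The fit was a Cox model with time-varying exposure coded as the plan states. No baseline confounder was built in, so baseline adjustment could not help.

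All rates are assumptions:
- progression 2% per month;
- death 0.6% per month before progression, ×5 after it (×3 in one scenario);
- stopping 1% per month before progression;
- starting 10% or 3% per month before progression.

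The stop and start columns give the multiplier after progression. There was no restarting, and switching between drugs was not simulated.

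| Stop | Start (base) | Plan's coding | Stratified on current progression | 3-month lag | 6-month lag | Ever treated | Landmark 6 / 12 months |
|---|---|---|---|---|---|---|---|
| ×1 | ×1 (10%) | 1.01 | 1.02 | 1.01 | 1.02 | 1.02 | 1.00 / 1.01 |
| ×3 | ×1 (10%) | 0.78 | 0.99 | 0.81 | 0.83 | 0.96 | 1.01 / 0.97 |
| ×10 | ×1 (10%) | 0.54 | 1.01 | 0.60 | 0.64 | 0.98 | 0.97 / 0.86 |
| ×10, death ×3 | ×1 (10%) | 0.64 | 1.00 | 0.69 | 0.73 | 1.03 | 0.96 / 0.90 |
| ×10 | ×3 (10%) | 0.56 | 1.01 | 0.62 | 0.68 | 1.52 | 1.07 / 0.94 |
| ×10 | ×5 (3%) | 0.77 | 1.01 | 0.86 | 0.95 | 1.87 | 1.15 / 1.12 |
| ×3 | ×5 (3%) | 1.12 | 0.99 | 1.18 | 1.24 | 1.79 | 1.13 / 1.19 |
| ×1 | ×5 (3%) | 1.46 | 1.00 | 1.49 | 1.52 | 1.80 | 1.17 / 1.24 |

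**Reading the table.**
1. With stopping and starting unrelated to progression there is no bias (1.01). The coding rule does harm only through its link with prognosis.
2. Progression-driven stopping alone gives 0.54 to 0.78. When progression-driven starting dominates, the result is 1.12 to 1.46.
3. Accounting for current progression gives 0.99 to 1.02 in all eight scenarios. Simple stratification suffices here because the drug does not affect progression. If it does, conditioning on progression removes part of the drug's own effect, and weighting is needed instead.
4. A lag removes only part of the bias from stopping (0.54 becomes 0.60 or 0.64) and enlarges the bias from starting (1.12 becomes 1.18 or 1.24). Ever-treated coding works only if starting is unrelated to progression. Otherwise it gives 1.52 to 1.87.
5. In the seventh row the main model (1.12) and the landmarks (1.13, 1.19) agree, and all are wrong. Convergence is therefore not evidence against this confounding.

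**Switches.** By the same reasoning, the drug left at progression sheds its high-risk time and looks better, and the drug switched to receives that time and looks worse.

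**The case against.** A reader might infer that under this rule any drug looks protective. The documents do not support that. They give no rates of starting, stopping or progression; the sign reverses when progression prompts starting; and deaths after a switch count against the new drug, not against no treatment.

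A reader might also infer that the plan says patients stop because they progress. It says so of switches only. For stopping, the sole link is that it is handled analogously, which may refer just to the interval mechanism.

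A third inference would be that a short carry-forward of exposure cures the problem. It does so only if the deterioration that prompts the stop leads to death within the lag. Simulations that assume stops 2 to 12 weeks before death are put right by a 13-week lag by construction. The table shows only partial repair when progression comes earlier.

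Four further points favour the plan:

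- The covariate list is introduced as inclusive and informed by a causal diagram, so it is not expressly closed. That stands, but every item named is a baseline characteristic or a comorbidity.
- Detail may sit in a full analysis plan that is not shown. The article nevertheless fixes the coding rule, the sensitivity analyses and the robustness criterion, and these can be judged as written.
- The landmark analysis is not worthless. Where only stopping depends on progression it gave 0.86 to 1.01 against 0.54 to 0.78, so it would tend to diverge and give a warning. The plan does not say what follows from divergence.
- The estimates are labelled exploratory. This lowers the consequence, but the label is tied to the two named limitations and does not alert readers to this bias.

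**Conclusion.** The concern holds in a bounded form. As written, the plan lets treatment changes that may follow progression move high-risk time between exposure groups, pools previously treated with never-treated time, and names no method for the resulting confounding. For a drug with no effect, the hazard ratio was about 0.5 to 0.8 or about 1.1 to 1.5, depending on whether stopping or starting was tied more strongly to progression. These values illustrate assumed rates and do not predict what this registry will find. If treatment changes are unrelated to prognosis, there is no bias.

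Severity is moderate. Treatment-specific outcomes are secondary and their comparative estimates are already called exploratory. Overall survival described without a treatment comparison does not depend on the exposure coding.

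**What to change.** 1. **Add a model for time-updated severity** to the comparative survival analyses, for example a marginal structural Cox model with stabilised weights. By the follow-up sections of the article, NYHA belongs to the minimal core dataset for ATTRv, ATTRwt, AL and AA amyloidosis, and NIS to that for both ATTR forms. NT-proBNP and renal function are not in any minimal core, so use them where available.
2. **Code time after stopping as a separate previously-treated state**, not pooled with never-treated or not-yet-treated time. Report lagged exposure (for example 30, 90 and 180 days) and ever-treated coding as sensitivity analyses only, since neither removes the bias in general.
3. **Limit the landmark robustness statement to immortal-time bias**, and list progression-driven stopping and switching as a third limitation.

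The cost is wording in the analysis plan and additional R code, with no new data collection. Weighting will widen intervals, and the weights will rest on irregularly timed measurements because visits are clinically driven. Lagging also dilutes the exposure contrast somewhat.

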### AA amyloidosis follow up

AA amyloidosis can have various clinical presentations and disease courses, depending on the underlying disease [14]. Follow-up is therefore generally performed on an individual basis but includes structured data collection at least yearly as shown in Fig 8. The minimal core dataset for AA amyloidosis follow-up consists of a structured medical history/NYHA (Fig 8, Medical history; [a] in cardiology).

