### Data collection and management

After patient selection and written informed consent, upon registration in our research database (Tbase), each participant is assigned an ongoing number as pseudonymization code. Data is stored using the digital interoperable Tbase platform developed in the clinic as part of research efforts. Keys for patient re-identification is stored within the Tbase platform only accessible by the research personal. The Tbase research database is located within the secure environment of Charité – Universitätsmedizin Berlin, featuring encryption during transmission and storage, role-based access control, and audit logs.

To collect patient reported outcomes (PROMs) more efficiently, a patient facing smartphone application called dotbase (a digital medical workspace designed for clinical environments, dotbase medical GmbH, Berlin, Germany. Available at: https://dotbase.org) is used, allowing collection of questionnaires from outside of the clinic. Third-party digital tools (dotbase, Tbase) are based on specific collaboration agreements and technology is hosted in Germany. Data access is completely restricted to and hosted by Charité – Universitätsmedizin Berlin. All data access is logged and changes are trackable. Patient recruitment, data flow and distribution are visualised in Fig 9. During clinical visits, physicians directly input data into the electronic database (Tbase). Here, data from the electronic health record (EHR), e.g., laboratory results, imaging, and functional examinations, are included automatically. Data items were selected according to clinical relevance and agreed upon core data sets. The resulting information is combined with patient reported outcomes and additional information such as type of referring physician or date of earliest symptoms.

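### The landmark analyses are said to avoid immortal-time bias by construction, but nothing limits landmark treatment status to records made by the landmark; at 6 months this can fail for sparsely seen patients

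*Protocol article*

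**What the plan says.** The Statistical analysis plan section models treatment as a time-varying covariate and adds a sensitivity analysis in which "a landmark approach will be applied at 6 and 12 months, classifying patients by treatment status at the landmark and restricting follow-up accordingly". The reason given is stated as fact: "as this approach avoids immortal-time bias by design rather than by statistical adjustment". The result then has a defined use: "convergence of results with the primary analysis will serve as an indicator of robustness".

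The same paragraph describes how the exposure data arise. It says that "treatment event dates are recorded at clinical visits rather than to the exact calendar day" and that "the frequency and timing of follow-up visits are clinically driven rather than protocol-fixed", and it accepts that changes between visits may not be fully captured. A ±4-week window around documented dates is offered for the first of these two limitations only. The Data collection and management section has physicians entering data at the visit.

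Visit spacing differs by subtype. AL patients are seen every 2 weeks at first and every 3 months when stable. AA follow-up is "generally performed on an individual basis but includes structured data collection at least yearly as shown in Fig 8". Neurological follow-up in ATTRwt is every 12 months. The ATTRwt cardiology and ATTRv intervals are in Figs 5 and 6, which were not available for this review.

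**The concern.** A landmark analysis removes immortal time because group membership is fixed by what is known at the landmark. If membership is settled by information that arrives later, and arrives only for patients still alive, the protection is lost.

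Take a patient seen yearly who starts treatment in month 4. The start may first be recorded at the month-12 visit. If it is entered with its month-4 date, the patient counts as treated at 6 months. A second patient with the same start who dies in month 9 never has it recorded and counts as untreated. Between months 6 and 12, every patient classified as treated through such a record is alive by construction.

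The time-varying Cox model uses the same dates and has the same weakness. The two analyses can therefore agree because they share an error, and the plan would read that agreement as robustness.

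**Working it through.** The plan gives no figure for this point, so there is none to reproduce. The check asks how large the effect could be when treatment does nothing.

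**From the document:** landmarks at 6 and 12 months; treatment dates captured at visits; a yearly minimum for AA.

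**Assumed, not in the document:** constant death rate *h* per year; a share *b* of patients with treatment recorded at enrolment; of the rest, 60% start uniformly over 24 months, so the share started by month 6 is p = 0.60 × 6/24 = 0.15; first follow-up visit at month 12; starts back-dated if the patient reaches that visit and otherwise unknown; 36 months of follow-up from the landmark.

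**Per person alive at month 6:**
- Treatment recorded at enrolment, or truly not started: deaths 1 − e^(−3h); person-years (1 − e^(−3h))/h.
- Started and reached the visit, share (1−b)·p·e^(−0.5h): deaths 1 − e^(−2.5h); person-years 0.5 + (1 − e^(−2.5h))/h. Labelled treated.
- Started but died before the visit: per starter, 1 − e^(−0.5h) deaths and (1 − e^(−0.5h))/h − 0.5e^(−0.5h) person-years. Labelled untreated.

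**h = 0.10, b = 0**
- Treated rate: 0.2212 / 2.712 = 0.0816.
- Untreated rate: (0.85 × 0.2592 + 0.15 × 0.0488) / (0.85 × 2.5918 + 0.15 × 0.0121) = 0.2276 / 2.2048 = 0.1032.
- Ratio: 0.0816 / 0.1032 = 0.79, where the truth is 1.

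**h = 0.10, b = 0.5**
- Treated rate: (0.5 × 0.2592 + 0.075 × 0.9512 × 0.2212) / (0.5 × 2.5918 + 0.075 × 0.9512 × 2.712) = 0.1454 / 1.4894 = 0.0976.
- Untreated rate: (0.425 × 0.2592 + 0.075 × 0.0488) / (0.425 × 2.5918 + 0.075 × 0.0121) = 0.1138 / 1.1024 = 0.1032.
- Ratio: 0.95.

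**Other death rates.** For h = 0.05, 0.20 and 0.40 the same formulas give 0.80, 0.77 and 0.73 with b = 0, and 0.95, 0.94 and 0.93 with b = 0.5. Simulated Cox models (200,000 patients per setting, mortality 5% to 40% per year, visit at month 12 or spread over months 10 to 14) give 0.71 to 0.81 and 0.93 to 0.95.

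**When the problem goes away**
- Visit on the landmark: the gap is zero, the third group is empty and the ratio is 1. Simulation gives 0.99 to 1.02. Visits every 3 or 6 months give 0.99 to 1.01.
- 12-month landmark: 1.00 to 1.02 with the visit at month 12; 0.93 to 1.01 with visits over months 10 to 14; 0.92 to 1.00 if visits slip to months 12 to 14.
- Starts dated to the visit: 0.99 to 1.01 where estimable, so no immortal time. But the treated share at month 6 is 50% instead of about 57% (b = 0.5), or 0% instead of 15% (b = 0).
- Status taken only from entries made by the landmark (b = 0.5): 1.00, because both groups then die at rate *h*.

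**The primary model on the same data.** Simulated time-varying rate ratios under back-dating and yearly visits, with mortality 5% to 20% per year and follow-up to month 42 from enrolment, are 0.67 to 0.69 with b = 0 and about 0.82 with b = 0.5. Both analyses point to a benefit that does not exist.

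**The ±4-week window.** From a 6-month landmark to a 12-month visit is about 26 weeks. Shifting documented dates also cannot restore starts that were never documented.

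**The case against.** The strongest reply is that the damaging mechanism needs back-dating, which the document does not state. A reader might infer that immortal-time bias definitely returns. The text does not support that: if the visit date is the recorded date, the result is misclassification, which dilutes a real effect and creates no false one.

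The affected group is also narrow on the visible text. Yearly is a minimum for AA, the 12-month interval in ATTRwt concerns neurology only, AL is seen far more often, and some schedules are in figures not available here. Starts also have other routes into the registry: therapy is among the key data entered in Tbase, and the weekly case conference covers treatment initiation and its written record is stored. A start agreed there would leave a dated entry that survives an early death.

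Two further inferences go too far. One is that the 12-month landmark has the same fault; a visit held by month 12 leaves nothing to be recorded afterwards. The other is a ratio near one half. Values of 0.51 to 0.54 arise only if 40% start before the landmark, none of those starts is recorded before a yearly visit, and follow-up stops at month 24.

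Finally, the plan admits imprecise dates and missed changes and labels its comparative estimates exploratory, and an article may leave record-level rules to a fuller plan.

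All of this limits the size and reach of the point. It does not rescue the claim, which is stated without condition and is the basis of the plan's own robustness criterion.

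**Conclusion.** The point holds in a limited form. The landmark analysis is free of immortal time only if status is taken from records made by the landmark. The plan does not require this, and its own account of data capture allows 6-month status to be recorded later. Which error follows depends on a dating rule the document does not give: back-dated starts produce a spurious benefit, visit-dated starts produce misclassification.

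Under back-dating with yearly visits, the 6-month ratio under the null is about 0.71 to 0.81, moving to 0.93 to 0.95 when half the patients have treatment recorded at enrolment. These figures rest on assumed mortality, uptake and visit timing and describe only patients seen yearly; the share of such patients is not given, so the effect in the whole registry would be smaller. The 12-month landmark is little affected unless visits slip. Agreement between the landmark and time-varying analyses is weaker evidence than the plan takes it to be, because both can err in the same direction. Severity is low to moderate: this is a sensitivity analysis of estimates already labelled exploratory.

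**What to change.** - Classify landmark status only from treatment records, whether visit or case-conference entries, that were entered on or before the landmark. The Data collection and management section says changes are trackable, so the entry date should be available as a filter.
- State whether a recorded start date is the visit date or a date reported at the visit.
- As a supplement for sparsely seen patients, add a landmark placed after the first annual visit window.
- Say that freedom from immortal time holds under these rules, and that agreement with the time-varying model counts as support only when that model's dates have been examined for the same problem.

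A requirement of a visit in the 3 months before the landmark should not be part of the main rule. Visit frequency is clinically driven, so the restriction selects on it; it could serve as a secondary check.

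The cost is a few sentences and one data filter. The downside is that some patients who start between visits will count as untreated at 6 months, which dilutes a real effect. If no treatment is recorded by the landmark in a yearly-seen group, the 6-month comparison cannot be estimated there, which is why the later landmark is useful.
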